#### Sample Size Calculation

As for the primary outcome of the study, namely, the MADRS score, we will use a standard deviation of 5.15 and a difference in the mean of 2.9 (M1 = 20.0, M2 = 17.1). We based our assumptions regarding the mean and standard deviation of MADRS in a depressed population on a study by Dijkstra et al. [49]. A difference in the MADRS of 2.2 points or higher seems clinically relevant (Cohen’s D has a value of 0.4, while a value of 0.4 or higher is widely considered to be associated with a clinically relevant effect size). Using an online tool (https://www.stat.ubc.ca/~rollin/stats/ssize/n2.html, accessed on 2 December 2022), we calculated the required sample size (assuming that both groups taking part in the study are the same size). The total sample size for this study should be around 100 (M1 = 20.0, M2 = 17.1, SD = 5.15, alpha = 0.05, power = 80%).

More details of sample size calculations for different secondary outcome measures are described in Appendix A.

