### 3.1. Patients

Study groups:

Group I “PRO-D”—patients with diagnosed depressive disorders; meeting the criteria of the International Classification of Diseases (ICD-11) for 6A70-73, 6A7Y, and 6A7Z; and taking a probiotic composed of two bacteria strains: *Lactobacillus helveticus Rosell* and *Bifidobacterium longum Rosell*. The severity of depression will be evaluated with the use of the Montgomery–Åsberg Depression Rating Scale (MADRS). The patient will be included in the group after obtaining 13 or more points.

Group II “PLC-D”—patients with diagnosed depressive disorders; meeting the criteria of the International Classification of Diseases (ICD-11) for 6A70-73, 6A7Y, and 6A7Z; and taking a placebo. The severity of depression will be evaluated similarly as in group I and patients will be enrolled after obtaining 13 or more points in the MADRS. In both groups, the authors will measure the patients’ severity of anxiety symptoms with the Depression, Anxiety, and Stress Scale (DASS) to further analyze patients according to their level of anxiety and stress.

The designed study will be prospective, randomized, placebo-controlled, and double-blind. The intervention period will last 8 weeks for each patient and the study will be conducted on 100 patients in total, who will be randomly divided into two groups, consisting of 50 patients each.

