1. Depressive disorders diagnosed according to the ICD-11; 2. Age between 18–70 years; 3. MADRS score > = 13; 4. Anti-depressant and anti-anxiety medications not changed within 3 weeks prior to the recruitment visit.	1. Pregnancy; 2. An infection/vaccination and/or treatment with antibiotics in the previous 4 weeks; 3. Supplementation with pro- or prebiotics in the previous 4 weeks; 4. Having a diagnosis of an autoimmune disease, being seriously immunocompromised, inflammatory bowel disease, cancer, IgE-dependent allergy, or severe kidney failure in the previous 4 weeks; 5. BMI > 35; 6. GFR < 30 mL/min/1.72 m^2^; 7. Unstable thyroid dysfunction (TSH < 0.27 or >4.2 µIU/mL) in the previous 4 weeks; 8. Psychiatric comorbidities (except specific personality disorder, additional specific anxiety disorder, and caffeine and nicotine addiction); 9. Regular treatment (more than 3 days a week) with PPIs, metformin, laxatives, systemic steroids, or NSAIDs in the previous 4 weeks; 10. Significant change in dietary pattern in the previous 4 weeks; 11. Significant change in daily physical activity or undertaking an extreme sports activity in the previous 4 weeks; 12. Significant change in dietary supplementation in the previous 4 weeks; 13. Significant change in smoking pattern in the previous 4 weeks; 14. High risk of suicide; 15. Is participating in, or has recently participated in, another research study involving an intervention that may alter the outcomes of interest for this study; 16. Any other condition or situation which, in the view of investigators, would affect the compliance or safety of the individual taking part.	1. Withdrawal of informed consent; 2. An infection/vaccination and/or treatment with antibiotics during the trial; 3. Consuming any probiotics other than those studied during the trial; 4. Lack of compliance with the probiotic supplementation; 5. Any change in the drug regimen during the study; 6. Exclusion criteria found after enrolment; 7. Any serious adverse event during the trial.

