## Figures and Tables

**Table 1 metabolites-13-00182-t001:** Primary and secondary outcome measures. BMI: body mass index; BP: blood pressure; CRP: C-reactive protein; DASS: Depression, Anxiety, and Stress Scale; fGlc: fasting glucose; HDL-c: high-density protein cholesterol; MADRS: Montgomery–Åsberg Depression Rating Scale; MC: microbiota composition; MDA: malondialdehyde; SCFAs: short-chain fatty acids; TAC: total antioxidant capacity; TG: triglycerides; WBC: white blood cells; WC: waist circumference; WHOQOL-BREF: The World Health Organization Quality of Life-BREF.

	Materials and Methods			
	Psychometric Tools	Biological Samples		Physical Examination
		Blood	Feces	
Primary outcome measures				
Depressive symptoms	MADRS			
Secondary outcome measures				
Anxiety symptoms	DASS			
Stress level	DASS			
Quality of life	WHOQOL-BREF			
Metabolic parameters		fGlc, HDL-C, TG		BP, BMI, WC
Microbiota function			MC, SCFAs	
Inflammations parameters		WBC, NEU, CRP		
Oxidative stress parameters		TAC, MDA		

**Table 2 metabolites-13-00182-t002:** Depressive disorders in the ICD 11.

Depressive Disorders in the ICD 11	Code
Single-episode depressive disorder	6A70
Recurrent depressive disorder	6A71
Dysthymic disorder	6A72
Mixed depressive and anxiety disorder	6A73
Other specified depressive disorders	6A7Y
Depressive disorders, unspecified	6A7Z

**Table 4 metabolites-13-00182-t004:** The list of the recent clinical trials that demonstrated the efficacy of *Bifidobacterium longum* and *Lactobacillus helveticus* toward depressive, anxiety, and stress symptoms.

The List of the Recent Clinical Trials That Demonstrated the Efficacy of *Bifidobacterium longum* and *Lactobacillus helveticus* toward Depressive, Anxiety, and Stress Symptoms				
The Authors	Animal/Human Studies	Duration	Population	Results
Kazemi et al., 2018 [53]	Humans	8 weeks	110 depressed patients	”A significant decrease in BDI score (17.39–9.1) compared to the placebo (18.18–15.55) and prebiotic (19.72–14.14) supplementation (*p* = 0.042)”.
Romijin et al., 2017 [54]	Humans	8 weeks	79 participants (10 dropouts) with at least moderate scores on self-report mood measures	No significant impact on any psychological outcome measure.

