## Appendix A

Sample size analysis details:

The authors made an effort to determine the correct sample size for the study regarding the secondary endpoints.

As for CRP, the investigators in this study decided to use the number of participants needed to detect a mean difference between the groups in the hsCRP level of 2.0 mg/L (standard deviation 3.0 mg/L) at day 60 with 80% power and 95% confidence. The number of subjects needed was 20 per group. The range of values for the mean CRP and standard deviation in the group of depressed patients was indicated in the studies by Chamberlain et al. and Pitharouli et al. [76,77].

As for BMI, the sample size calculations were based on the assumption of a 2.0 kg/m^2^ reduction in BMI at day 60 in the probiotic group compared with the placebo group (M1 = 23.0, M2 = 21.0). A decrease in BMI by approximately 2 kg/m^2^ may significantly influence metabolic risk [78]. To detect this difference, assuming a common standard deviation of 3.0 using a two-group *t*-test with a 0.05 two-sided significance level, we estimated that a sample size of 20 subjects in the probiotic intervention group and 20 subjects in the placebo group would have 80% power.

As for the lipid profile, we determined that 16 participants in each study group (probiotic versus placebo) would be sufficient to detect a mean difference in LDL cholesterol of 0.45 mmol/L (M1 = 3.45 mmol/L, M2 = 3.0 mmol/L, SD = 0.6 mmol/L), with 80% power at *p* = 0.05. Hypothetical values were based on the data found in the study by Ivey et al. [79].

As for the first criterion of metabolic syndrome, namely, WC, we used a standard deviation of 8.5 and a difference in mean of 9.0 (M1 = 90.0 cm, M2 = 99.0 cm). We based our assumptions on a study by Niyonsenga et al. [80], which indicated a mean and standard deviation of WC in a depressed population. This calculation determined that 16 patients for each group were required to provide >80% power with *p* = 0.05.

As for HDL, we used a standard deviation of 11.6 and a difference in mean of 12.0 (M1 = 67.0 mg/dL, M2 = 55.0 mg/dL). We based our assumptions on a study by Martinac et al. [81], which provided a mean and standard deviation of HDL in a depressed population. This calculation determined that 16 patients for each group were required to provide >80% power with *p* = 0.05.

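### The 100 patients that give 80% power are patients with an analysed MADRS, yet exactly 100 are randomised with no allowance for loss

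*Protocol article*

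**What the plan says.** Section 2.4, under Sample Size Calculation, sets out the primary-outcome sizing in full. For MADRS it takes "a difference in the mean of 2.9 (M1 = 20.0, M2 = 17.1"), says "we will use a standard deviation of 5.15", assumes equal groups, and lists "alpha = 0.05, power = 80"%. It concludes: "The total sample size for this study should be around 100". No attrition term appears among these inputs.

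Section 3.1 fixes enrolment at the same number: "the study will be conducted on 100 patients in total, who will be randomly divided into two groups", with 50 patients in each.

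Three other places bear on how many of the 100 will have a post-treatment MADRS:

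- The third column of Table 3 gives seven reasons for discontinuing a participant from the study. One is "An infection/vaccination and/or treatment with antibiotics during the trial". Others are any change in drug regimen, lack of compliance, other probiotics and withdrawal of consent.
- Section 3.2 places the post-treatment MADRS at V2, 8 weeks after randomisation.
- Table 4 describes one 8-week human trial as having "79 participants (10 dropouts) with at least moderate scores on self-report mood measures".

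The Discussion names the size of the trial as a limitation but does not mention attrition.

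**The concern.** A two-sample formula returns the number of patients who contribute an outcome to the comparison. Here that number and the number randomised are the same, so any loss of week-8 MADRS data takes power below the stated figure. An allowance held in another document could not fit inside 100 randomised patients without leaving fewer than 100 analysed.

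At stake is how a non-significant primary result would be read. Someone told that the trial had 80% power for 2.9 points would give a null result more weight than it deserves if the power for that difference was nearer 70 to 75%. The Discussion adds to the risk by saying that the sample size is enough to detect statistical significance.

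**Working it through.** **Inputs.** Difference 2.9, SD 5.15, alpha 0.05, power 80% and 1:1 allocation come from the Sample Size Calculation section. The number randomised, 50 per arm, comes from section 3.1. The test's sidedness is not stated for MADRS. Two-sided is assumed because it reproduces the stated total (one-sided gives 39 per arm), and Appendix A sizes BMI "with a 0.05 two-sided significance level". The article gives no loss rate for this trial. The rate of 10/79 = 12.7% is from Table 4; the 5%, 10% and 20% rates are assumptions.

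**Step 1: reproduce the plan's figure.** Normal approximation, per arm:

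n = 2 × [SD × (1.960 + 0.842) / difference]² = 2 × [5.15 × 2.802 / 2.9]² = 49.5, rounded up to 50, so 100 in total.

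The stated total reproduces. The t-test needs 50.5, that is 51 per arm. At 50 per arm, power is 80.4% by the normal formula and 79.6% by the t-test. There is no spare patient to lose.

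**Step 2: power after loss.** With loss L equal in both arms, n = 50 × (1 − L) per arm. The standard error of the difference is 5.15 × √(2/n), and the noncentrality is 2.9 divided by that. At L = 20%, n = 40, the standard error is 5.15 × √(2/40) = 1.152, and the noncentrality is 2.9 / 1.152 = 2.52. Two-sided t-test power is then 70.1%. The detectable difference is the one that gives 80% power at the same n.

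| Loss by week 8 | Source of rate | Analysed per arm | Power for 2.9 | Difference detectable at 80% |
|---|---|---|---|---|
| 0% | implicit in the plan | 50 | 79.6% | 2.9 |
| 5% | assumed | 47.5 | 77.5% | 3.0 |
| 10% | assumed | 45 | 75.2% | 3.1 |
| 12.7% | Table 4, 10/79 | 43.7 | 73.9% | 3.1 |
| 20% | assumed | 40 | 70.1% | 3.3 |

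The normal approximation gives values about one point higher (76.2% at 10% loss, 71.2% at 20%).

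**Step 3: could baseline adjustment make up the loss?** Adjusting for baseline MADRS with baseline-to-final correlation r multiplies the SD by √(1 − r²). At r = 0.5 the SD is 5.15 × √0.75 = 4.46. Power for 2.9 from the t-test with that SD:

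| Loss | r = 0.3 | r = 0.4 | r = 0.5 |
|---|---|---|---|
| 12.7% | 78% | 81% | 85% |
| 20% | 74% | 77% | 82% |

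So the answer depends on r, and all three values of r are assumptions.

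**The case against.** The case on the other side has five parts.

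- **The calculation is right.** This stands. The article claims that about 100 follows from its inputs, and it does. A reader might infer a miscalculation, but the documents do not support that. The fault lies in using the result as the number to randomise.
- **The shortfall depends on a loss rate the trial does not give.** This also stands. The 12.7% is one row of Table 4, from a population chosen on self-report mood scores, and the row does not say whether the 10 dropouts lacked a final outcome. A reader might infer from Table 3 that losses will be frequent, or count them over the whole 20 weeks of observation. Table 3 lists reasons, not frequencies, and the post-treatment MADRS is at 8 weeks.
- **A baseline-adjusted analysis might restore 80%.** The abstract defines the primary endpoint as a change in MADRS, and the model may be set out in an analysis plan not shown. So the flat statement that 80% power will not be delivered goes too far. Nor is the rescue assured: at 20% loss it works at r = 0.5 but not at r = 0.3 or 0.4. The published sizing uses the raw SD and no correlation.
- **Replacement of patients, or follow-up after discontinuation, may be covered in the full protocol.** That is possible, and their absence from a condensed article is not held against it. But Table 3 speaks of discontinuation from the study, and the article gives the sizing in full with its required and randomised numbers equal.
- **The Discussion already warns that the sample may be too small.** It does so in general terms. It neither mentions attrition nor qualifies the 80%.

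**Conclusion.** The concern holds in a conditional form. The sample-size arithmetic is correct, but it describes a trial that loses essentially no one by week 8, and the article's own tables make some loss foreseeable. For an unadjusted two-sample comparison at 2.9 points and SD 5.15, power is about 74% at the only loss rate in the article and 70% at an assumed 20%. The detectable difference rises from 2.9 to 3.1 and 3.3 points.

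These figures assume a two-sided 5% test, equal loss in both arms and an SD among those analysed equal to the planning SD. They show how far the stated power depends on complete data. They do not predict this trial's dropout, and they do not show that a baseline-adjusted analysis would fall short. The matter is worth correcting because the statement is incomplete as written and cheap to repair.

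**What to change.** Keep 100 patients. In the Sample Size Calculation section, say that 50 per arm is the number with an analysed week-8 MADRS. Then give power and detectable difference at the number expected to be analysed, with the loss rate labelled as an assumption. For example: for an unadjusted comparison, 100 randomised patients give 74% power for 2.9 points at 12.7% loss (detectable difference 3.1) and 70% at 20% loss (detectable difference 3.3).

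If the primary analysis will adjust for baseline MADRS and the power claim relies on that, say so and give the range: at 20% loss, 74% for r = 0.3, 77% for r = 0.4 and 82% for r = 0.5.

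The cost is one or two sentences and a slightly less favourable power statement; recruitment does not change. Keeping 100 analysed patients would instead mean randomising 100 / (1 − 10/79) = 114.5, so 116 for equal arms, or 100 / 0.80 = 125, so 126 for equal arms at 20% loss. That costs far more and is not needed to make the statement correct.

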## 3. Results

As a result of our investigation, we created a study design, which is presented below.

### 3.1. Patients

Study groups:

Group I “PRO-D”—patients with diagnosed depressive disorders; meeting the criteria of the International Classification of Diseases (ICD-11) for 6A70-73, 6A7Y, and 6A7Z; and taking a probiotic composed of two bacteria strains: *Lactobacillus helveticus Rosell* and *Bifidobacterium longum Rosell*. The severity of depression will be evaluated with the use of the Montgomery–Åsberg Depression Rating Scale (MADRS). The patient will be included in the group after obtaining 13 or more points.

Group II “PLC-D”—patients with diagnosed depressive disorders; meeting the criteria of the International Classification of Diseases (ICD-11) for 6A70-73, 6A7Y, and 6A7Z; and taking a placebo. The severity of depression will be evaluated similarly as in group I and patients will be enrolled after obtaining 13 or more points in the MADRS. In both groups, the authors will measure the patients’ severity of anxiety symptoms with the Depression, Anxiety, and Stress Scale (DASS) to further analyze patients according to their level of anxiety and stress.

The designed study will be prospective, randomized, placebo-controlled, and double-blind. The intervention period will last 8 weeks for each patient and the study will be conducted on 100 patients in total, who will be randomly divided into two groups, consisting of 50 patients each.

#### Randomization

The participants will undergo randomization and will be randomly allocated into two groups (probiotic or placebo treatment) in a 1:1 ratio by an independent researcher. Neither the subjects nor the investigators will be aware of the treatment assignment until the end of the trial. Randomization will be computed using a computer-based random number generator (https://www.randomizer.org/, accessed on 8 March 2021). The distribution of the pills will also be done by an independent researcher. The researchers agreed that unblinding should occur for the patient’s safety only if any serious adverse events occur during the investigation.

### 3.2. Design

The patients from the two clinical groups will undergo pharmacological and psychological treatment in compliance with the procedures of the clinic. It is worth mentioning that the researchers will at no stage interfere in the treatment process.

The patients will be recruited in the Central Teaching Hospital (inpatient and outpatient clinics), Medical University of Lodz, Poland.

We plan to measure the following metabolic parameters: blood pressure (BP), weight, body mass index (BMI), and waist circumference (WC). Blood samples of each patient will be collected to determine serum CBC and measure the levels of C-reactive protein, HDL cholesterol, triglycerides, and fasting glucose. Microbiota function (as SCFA concentrations in feces) and composition will be assessed. The oxidative stress level in the blood will be assessed as the total antioxidant capacity (TAC) and the level of malondialdehyde (MDA) concentration in blood plasma.

The patients will be observed for twenty weeks and they will be administered probiotic supplements for the first eight weeks.

The study will consist of the following visits:

V0 “recruitment visit”: assessment of inclusion and exclusion criteria, giving informed consent, a full psychiatric and somatic examination, filling in a survey questionnaire (SQ), and filling in the MADRS scale;

V1 “randomisation visit” (within 5 days following V0): filling in the DASS and WHOQOL-BREF scales; measuring BP, WC, and BMI; blood and stool collection; and • t1-t3:3/8 monitoring using personal contact via phone or e-mail every two weeks; 

V2 “final visit” after 8 weeks following V1: filling in MADRS, DASS, and WHOQOL-BREF scales; measuring BP, WC, and BMI; and blood and stool collection; 

V3 “follow-up visit” after 12 weeks following V2: filling in the SQ, MADRS, DASS, and WHOQOL-BREF scales and measuring BP, WC, and BMI.

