### 3.3. Interventions

At the beginning (V0), the patients will be asked to perform routine physical activity and not to modify their diet during the study. Patients included in group I (PRO-D) will receive one capsule daily containing a probiotic mixture at a daily dose of 3 × 10^9^ colony-forming units (CFU). The probiotic will be composed of two bacteria strains (*Lactobacillus helveticus Rosell^®^-52* and *Bifidobacterium longum Rosell^®^-175*), excipients (potato starch and magnesium stearate), and the capsule shell (made of hydroxypropylmethylcellulose). It will be ordered directly from the manufacturer (Sanprobi Stress^®^, Sanprobi Sp. z o. o., Sp. k., Szczecin, Poland). In our study protocol, we decided to use the combination of these two strains because both strains were studied in experimental and animal models and were found to improve emotional behavior in animals [50,51,52]. Clinical studies with healthy subjects and depressed patients showed inconclusive results [50,53,54,55,56]. We created a summative table with the list of the recent clinical trials with the efficacy of *Bifidobacterium longum* and *Lactobacillus helveticus* toward depressive, anxiety, and stress symptoms that could give the rationale for the combination of these two strains (Table 4). Interestingly, these two strains seem to also have specific effects on pro-inflammatory cytokine synthesis by reducing the level of pro-inflammatory cytokines, such as IL-1β, IL-6, and TNF-α, which may aid their antidepressant effect [57,58]. Moreover, recent study results suggested that Bifidobacterium species (spp.) positively correlated with both improved insulin resistance and obesity, and this might be associated with metabolic syndrome [59,60].

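### Inpatients and outpatients are pooled, and the plan names care setting neither as a stratification factor nor as a covariate; naming it is a cheap gain in precision.

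*Protocol article*

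**What the plan says.** All statements are in the protocol article.

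- **Recruitment (section 3.2, Design).** "The patients will be recruited in the Central Teaching Hospital (inpatient and outpatient clinics"). The same section leaves drug and psychological treatment to the clinic's usual procedures.
- **Allocation (Randomization, under section 3.1).** Participants "will be randomly allocated into two groups (probiotic or placebo treatment) in a 1:1 ratio by an independent researcher". "Randomization will be computed using a computer-based random number generator". No stratification factor or block is mentioned.
- **Arm size (section 3.1, Patients).** 100 patients, "who will be randomly divided into two groups, consisting of 50 patients each".
- **Covariates (section 2.4, Statistical Analysis).** Models are to be adjusted for age, diet, BMI and further confounders that are not listed. The sentence follows the microbiota association analyses. Care setting is not named.
- **Planning figures (Sample Size Calculation).** "we will use a standard deviation of 5.15 and a difference in the mean of 2.9 (M1 = 20.0, M2 = 17.1").
- **Stability of diet and activity.** Table 3 excludes patients with "10. Significant change in dietary pattern in the previous 4 weeks; 11. Significant change in daily physical activity" over the same period. Section 3.3 adds that "the patients will be asked to perform routine physical activity and not to modify their diet during the study".

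**The concern.** Care setting is known at entry and could plausibly predict outcome: background treatment is left to the clinic, and diet and daily activity may differ between ward and home. As described, the design neither balances setting between the arms nor removes its variance in the analysis. The trial is sized with no reserve, so any avoidable variance in MADRS comes directly out of power. The microbiota and metabolic outcomes may be affected in the same way.

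A separate question of consistency arises. The article relies on stable diet and activity before and during the trial but does not say how this applies to a patient recently admitted, or to one discharged within the 8 weeks.

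**Working it through.** **Inputs from the article:** difference 2.9, SD 5.15, alpha 0.05, 50 per arm. Sidedness is not stated with the MADRS calculation; a two-sided test reproduces the figure.

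**Assumed inputs, because the article gives neither:** inpatient share p = 20% to 50%, and a setting effect D = 2 to 5 points on the MADRS quantity that is compared between arms.

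**1. The plan's own figure.** n per arm = 2 × (1.960 + 0.842)² × 5.15² / 2.9² = 49.5, so 50 per arm and 100 in total. This agrees with "The total sample size for this study should be around 100 (M1 = 20.0, M2 = 17.1, SD = 5.15, alpha = 0.05, power = 80"%). Power at 50 per arm is 80.4% by the normal approximation and 79.6% by the noncentral t. The powers below use the noncentral t.

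**2. Chance imbalance without stratification.** With 100 patients, fixed arms of 50 and 100p inpatients, the number of inpatients in one arm is hypergeometric. The gap in inpatient share moves in steps of 4 percentage points.

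| Inpatient share p | SD of gap | P(gap ≥ 12 points) | P(gap ≥ 20 points) |
|---|---|---|---|
| 20% | 0.080 | 21% | 2% |
| 30% | 0.092 | 28% | 5% |
| 40% | 0.098 | 31% | 7% |
| 50% | 0.101 | 32% | 7% |

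A gap g shifts the observed MADRS difference by g × D. With D = 5, a 12-point gap shifts it by 0.6 and a 20-point gap by 1.0. With D = 2 the shifts are 0.24 and 0.4. Averaged over randomisations the shift is zero.

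**3. Effect on power.** The between-setting variance is p(1−p)D².

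- *Case B, 5.15 is a within-setting SD.* The unadjusted SD is √(5.15² + p(1−p)D²).
- *Case A, 5.15 is the total SD.* The SD after adjustment for setting is √(5.15² − p(1−p)D²).

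| p | D | B: unadjusted SD | B: unadjusted power | A: adjusted SD | A: adjusted power |
|---|---|---|---|---|---|
| 20% | 2 | 5.21 | 78.7% | 5.09 | 80.6% |
| 30% | 3 | 5.33 | 76.8% | 4.96 | 82.5% |
| 50% | 3 | 5.36 | 76.3% | 4.93 | 83.0% |
| 20% | 5 | 5.52 | 73.9% | 4.75 | 85.7% |
| 50% | 5 | 5.72 | 70.8% | 4.50 | 89.0% |

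In case B, adjusting for setting brings the SD back to 5.15 and power back to about 80%. In case A, the unadjusted analysis keeps the planned 80%.

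**4. Steps 2 and 3 describe one loss, not two.** The planned standard error is 5.15 × √(2/50) = 1.03. For p = 50% and D = 5, the SD of the shift from imbalance is 0.101 × 5 = 0.50. Then √(1.03² + 0.50²) = 1.15, which matches 5.72 × 0.2 = 1.14 from case B up to rounding. The standard error of the unadjusted test already contains the chance imbalance.

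**The case against.** **Silence is not a statement.** The article never says that the allocation is unstratified. A condensed article may leave strata, blocks and the covariates of the primary model to the full protocol. The open-ended part of the covariate list could also include setting. This stands as a limit: the point concerns the design as described. Still, the article has a dedicated randomisation section, and its covariate sentence is attached to the microbiota analyses.

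**The entry rules may leave few inpatients and a small contrast.** Table 3 requires antidepressant and anti-anxiety drugs unchanged for 3 weeks, excludes high suicide risk, and discontinues a patient whose drug regimen changes. This stands. No figure in the article shows setting to be a strong predictor, and 5 points is nearly one SD. The abstract also defines the endpoint as change in MADRS, so a stable severity gap between settings would largely cancel.

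**Simple randomisation is valid.** Correct. A reader might infer that imbalance in setting would bias the result. It would not: the error has mean zero, and type I error is unaffected.

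**Are the plan's own diet and activity rules broken?** A reader might infer that admission and discharge violate them. The article does not support this. The entry rule bars a significant change in the previous 4 weeks, so it screens out a recently admitted patient whose diet or activity changed significantly. The in-study rule is a request and is not among the reasons for discontinuation. Nor does this tension cause imbalance between arms: a change at discharge adds variance even when the arms are perfectly balanced, and stratifying at V1 would not remove differences in discharge timing.

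**Conclusion.** The point holds as a cheap improvement of low to moderate severity. Two care settings are recruited, and the described allocation and analysis name setting nowhere. If setting is prognostic, the cost is precision only.

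Over the assumed range (20% to 50% inpatients, effect of 2 to 5 points), unadjusted power is about 71% to 79% if 5.15 is a within-setting SD. If 5.15 is the total SD, no planned power is lost, and adjustment would raise it from 80% to about 81% to 89%. For effects of 2 to 3 points the difference is only about 1 to 3 percentage points either way. It matters more only if the effect is larger and inpatients are a substantial share. The article does not settle which reading of 5.15 applies.

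The passages on stable diet and activity are unreconciled with inpatient recruitment. That is a matter of clarity, separate from the precision argument.

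**What to change.** 1. Have the independent researcher generate two permuted-block 1:1 lists, one for inpatients and one for outpatients, by setting at V1.
2. Prespecify setting at V1 as a covariate in the between-arm models for MADRS and for the secondary outcomes. The MADRS baseline is the V0 score, because section 3.2 lists MADRS at V0, V2 and V3 but not at V1.
3. If randomisation has already begun, leave the allocation as it is and make the covariate adjustment alone.
4. Reconcile exclusion criteria 10 and 11 in Table 3 and the request in section 3.3 with the recruitment of inpatients, so that it is clear how they apply around admission and discharge. Which rule is right is for the investigators.

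The cost is one more list, one model term and possibly a slight departure from exactly 50:50. Sample size, blinding and treatment do not change.
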